### Follow-up

Outpatient follow-up will take place at specific time points for a total duration of 1 year; measurements performed during follow-up visits are depicted in figure 1.

### Adverse events

AEs will be recorded in detail in the electronic patient record. Any SAEs that occur after joining the trial will be reported to the accredited Medical Ethics Committee of our institution according to national and institutional guidelines. All AEs will be followed up until they have abated or until a stable situation has been reached. Depending on the event, follow-up may require additional tests or medical procedures as indicated and/or referral to a general physician or medical specialist. An interim analysis after 10 patients will be performed. If SAEs in these 10 patients have occurred, we will discuss the continuation of the study. The study will be prematurely terminated if two or more intracranial bleedings occur or more than five allergic reactions.

### Statistical analysis

Categorised epidemiological/descriptive patient variables are summarised with frequencies and will be analysed with Fischer’s exact test or Pearson’s χ^2^ test. To avoid possible violations of the assumptions for parametric testing, such as a normal distribution pattern, we will employ non-parametric methods such as Spearman’s rank correlation and Mann-Whitney U test in the case of a skewed distribution or log transformation. For associations of two outcome measurements, we will use a correlation (Spearman’s rank) or single regression analysis. We will analyse the following outcomes by means of Kaplan-Meier curves: patency rate, amputation-free rate and intervention-free rate. We will assess heterogeneity in prognostic factors as a secondary analysis by means of χ^2^ tests. All tests will be performed two-sided, and p<0.05 will be considered to be statistically significant.

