### Primary study parameters

Main end points will be the safety and technical feasibility of the experimental treatment. Safety will be determined by treatment-related mortality, the occurrence of adverse events (AEs), serious adverse events (SAEs) and suspected unexpected serious adverse reactions (SUSARs). AEs will be defined as any undesirable experience occurring to a subject during the experimental treatment period, whether or not considered to be related to the investigational drug or intervention. SAEs will be defined as any untoward medical occurrence or effect that at any dose results in death; is life threatening (at the time of the event); requires hospitalisation or prolongation of existing in-patients’ hospitalisation; results in persistent or significant disability or incapacity; is a new event of the trial likely to affect the safety of the subjects, such as an unexpected outcome of an adverse reaction. SUSARs, which are related to the microbubble infusion and ultrasound application, are the formation of microemboli resulting in occlusion of the microcirculation, haemorrhages, hypotension, heart rhythm disorders and anaphylaxis. See the section ‘Adverse events’ for detailed handling procedures of AEs, SAEs and SUSARs. Haemorrhagic complications related to thrombolytic therapy will be reported according to the Standardized Bleeding Definitions for Cardiovascular Clinical Trials proposed by Mehran *et al*.^12^

Technical feasibility will be defined as accomplishment of the experimental protocol during the first hour of thrombolysis.

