### Secondary study parameters

Angiographic success will be defined as dissolution of >95% of the thrombus with outflow to at least one crural artery. Clinical change/success will be reported according to Rutherford’s recommended scale for gauging changes in clinical status (table 1). Amputations will be defined as either major (above or below knee amputation) or minor (metatarsal or toe amputation). Additional interventions will be categorised as either surgical (eg, thromboembolectomy, bypass graft surgery) or percutaneous (percutaneous transluminal angioplasty, stent placement) and as either required for restoration of patency or necessary for correction of underlying lesions. We will also determine microcirculation of the limb (by Laser Doppler measurements, Perimed Instruments, Järfälla, Sweden), 30-day mortality, conversion to surgery, serum fibrinogen concentrations measured during thrombolytic treatment on a daily basis, pain by visual analogue scale (VAS) and quality of life by SF-36 questionnaires. The duration of thrombolysis will be defined by the time span between initiation and completion angiography.

**Table 1 T1:** Rutherford’s^24^ recommended scale for gauging changes in clinical status

+3	Markedly improved: no ischaemic symptoms and any foot lesions completely healed; ABI essentially ‘normalised’ (increased to >0.90)
+2	Moderately improved: no open foot lesions; still symptomatic but only with exercise and improved by at least one clinical chronic ischaemia category; ABI not normalised but increased by >0.10
+1	Minimally improved: >0.10 increase in ABI* but no categorical improvement or vice versa (ie, upward categorical shift without an increase in ABI of >0.10)
0	No change: no categorical shift and <0.10 change in ABI
−1	Mildly worse: no categorical shift but ABI decreased >0.10 or downward categorical shift with ABI decrease <0.10
−2	Moderately worse: one category worse or unexpected minor amputation
−3	Markedly worse: more than one category worse or unexpected major amputations

*In cases where the ABI cannot be accurately measured, an index based on the toe pressure, or any measurable pressure distal to the site of revascularisation, may be substituted.

ABI, Ankle Brachial Index.

Adapted from Rutherford RB et al. JVS 1997.

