### Patients and eligibility criteria

The present feasibility and safety study is a non-randomised phase II trial to be conducted in our university hospital in Amsterdam, the Netherlands. Usually, in a phase II trial 10–20 patients are investigated to confirm an occurrence of toxic effects or SAEs<20%. We chose a sample size of 20 to assess the safety of the investigational treatment. Eligibility criteria are listed in table 2. Inclusion of 20 eligible patient is expected within 1.5 years. Written informed consent will be acquired by a member of the Research Team after information about the study has been provided by the treating doctor.

**Table 2 T2:** Eligibility criteria

Inclusion criteria	Men and women older than 18 and younger than 85 years Patients with a maximum of 2 weeks of symptoms for lower limb ischaemia due to thrombosed/occluded iliofemoral, femoropopliteal or femorocrural native arteries or iliofemoral, femoropopliteal or femorocrural venous or prosthetic bypass grafts Patients appropriate for thrombolysis, that is, with acute lower limb ischaemia class I and IIa according to the Rutherford classification Patients who understand the nature of the procedure and provide written informed consent before enrolment in the study

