If the application of microbubbles and ultrasound concomitant to catheter-directed thrombolysis is shown to be safe and technically feasible based on this phase II trial, we anticipate a funding application for a larger randomised controlled trial with a comparative group to assess and compare efficacy of this treatment.

Although the efficacy of the currently described protocol cannot be adequately compared within this study design, we will discuss the outcomes relative to a historic control group that had previously received our standard hospital thrombolysis protocol.^22^

Successful thrombolysis is strongly predictive of amputation-free survival with vascular patency for at least 1 year.^23^ A longer duration of thrombolysis inevitably exposes a patient to a higher thrombolytic dose and higher risk of haemorrhage, in addition to an already increased patient burden because of prolonged bed rest. Therefore ultimately, acceleration of thrombolysis with microbubbles could benefit the patient because of a shorter therapy time, a lower risk of haemorrhagic complications and a decrease in patient burden.

10.1136/bmjopen-2016-014365.supp2Check list

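### Kaplan-Meier is named for patency, amputation-free and intervention-free rates although death precludes each event; a cumulative-incidence estimator and a labelled amputation-free survival curve would serve better (low priority)

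*Protocol article*

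**What the plan says.** The Statistical analysis section of the protocol article fixes one estimator for three outcomes: "We will analyse the following outcomes by means of Kaplan-Meier curves: patency rate, amputation-free rate and intervention-free rate". It does not say whether a death is an event, is censored or is a competing event.

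The Follow-up section sets the horizon: "Outpatient follow-up will take place at specific time points for a total duration of 1 year". Death is foreseen as an outcome. Treatment-related mortality is part of the safety end point (Primary study parameters), and the Secondary study parameters include "30-day mortality, conversion to surgery". No mortality or event rate is given for any of the three curves.

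The eligibility table admits patients up to the age of 85. It excludes malignancy or severe comorbidity when life expectancy is below 6 months, which is half the follow-up period. The sample size is 20 and was chosen for safety: "We chose a sample size of 20 to assess the safety of the investigational treatment".

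**The concern.** Kaplan-Meier estimates the probability of staying free of an event on the premise that a censored patient could still have it later. That premise fails for death, which precludes all three events. It also fails for major amputation of the treated limb, which precludes later loss of patency or re-intervention in that limb.

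Either way of handling death leaves a problem for these outcome names:

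- **Deaths censored.** One minus Kaplan-Meier is never below the proportion of patients who actually have the event, and lies above it once a death precedes a later event. The amputation-free rate describes freedom from amputation with deaths set aside.
- **Deaths counted as events.** Each curve is a valid event-free survival curve. Labelled as a patency rate or an intervention-free rate, however, it would present deaths as occlusions or re-interventions.

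So if deaths precede later events, neither version gives the proportion of patients re-intervened on or occluded by 1 year. At stake is how the curves are read. The Strengths and limitations list says the data will inform a later randomised trial, and the Discussion says outcomes will be set beside a historic control group.

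**Working it through.** The article gives no figure for these curves, so there is nothing to reproduce. The check measures the size of the effect under stated assumptions.

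**Inputs**
- From the article: 20 patients, 1 year of follow-up, Kaplan-Meier.
- Assumed: 1-year mortality d of 5–20% (1 to 4 deaths among 20 patients); net 1-year event risk m of 15–50%, meaning the value of one minus Kaplan-Meier with deaths censored; constant and independent hazards. Only death is treated as competing here.

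**Formulas**
- Hazards: h1 = −ln(1 − m) for the event, h2 = −ln(1 − d) for death.
- Cumulative incidence: CIF = h1/(h1 + h2) × [1 − exp(−(h1 + h2))].
- Event-free survival: exp(−(h1 + h2)) = (1 − m)(1 − d).
- Approximate standard error with 20 patients: √(m(1 − m)/20).

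**Re-intervention or loss of patency**
- *Smallest case, m = 15%, d = 5%.* h1 = 0.1625, h2 = 0.0513. CIF = 0.1625/0.2138 × 0.1925 = 14.6%. Overstatement 0.4 points; standard error 8.0 points.
- *Middle case, m = 30%, d = 15%.* h1 = 0.3567, h2 = 0.1625. CIF = 0.3567/0.5192 × 0.4050 = 27.8%. Overstatement 2.2 points; standard error 10.2 points, so the ratio is about 0.2.
- *Largest case, m = 50%, d = 20%.* h1 = 0.6931, h2 = 0.2231. CIF = 0.6931/0.9163 × 0.6000 = 45.4%. Overstatement 4.6 points; standard error 11.2 points, so the ratio is about 0.4.

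If deaths are counted as events in the middle case, the curve stands at 0.70 × 0.85 = 59.5%. Its complement of 40.5%, read as a re-intervention risk, is further from 27.8% than the death-censored 30.0%.

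**Amputation, m = 15%**
- Death-censored Kaplan-Meier shows 85.0% amputation-free.
- Amputation-free survival is 0.85 × 0.95 = 80.8% at 5% mortality, 0.85 × 0.85 = 72.2% at 15%, and 0.85 × 0.80 = 68.0% at 20%.
- The difference is 0.85 × d, or about 4 to 17 points.

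**Count example without a hazard model**

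Take 20 patients, 2 early deaths, 3 later amputations and complete follow-up otherwise.
- One minus Kaplan-Meier = 3/18 = 16.7%; actual incidence = 3/20 = 15.0%.
- Kaplan-Meier amputation-free = 83.3%; amputation-free survival = 15/20 = 75.0%.

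**The case against.** The strongest reply is that the error is inferred. The article never says that deaths are censored. Event definitions and censoring rules are commonly left to a full protocol or analysis plan, neither of which is shown, and if death is an event there is no competing-risk bias. This stands in part: the overstatement can only be claimed conditionally. It does not remove the point, because the estimator itself is stated, and counting deaths as events does not yield a re-intervention or patency figure either.

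The second reply is size. Every rate above is assumed, the bias stays under half a standard error, and the primary end points are safety and technical feasibility, on which the move to a randomised trial depends. This stands, and it sets the priority. Nothing in the article says that these curves will supply that trial's event rates.

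The third reply is that expected deaths are not documented. Mortality being an end point does not show that many deaths will occur, and short life expectancy with severe comorbidity is excluded. This is fair, and is why a range is shown.

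A reader might also infer that the Discussion uses amputation-free survival as the trial's benchmark, so that the amputation curve contradicts it. The text does not support this. The phrase "strongly predictive of amputation-free survival with vascular patency for at least 1 year" belongs to a cited background statement about successful thrombolysis. The stated comparison is with a historic control group whose outcome definitions are not given, and the plan never calls its own curve amputation-free survival.

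**Conclusion.** The point holds in conditional form. Kaplan-Meier is not the best estimator for re-intervention and loss of patency when death, or major amputation of the treated limb, can come first. If deaths are censored, the actual 1-year incidence is overstated by about 0.4–4.6 points, given constant independent hazards, 5–20% mortality and 15–50% net event risk. Under the same censoring, the amputation-free rate is not amputation-free survival and should not be read as such.

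Two stronger readings should be avoided. It is not established that the trial will overstate its event risks, because the handling of death is not stated. And the 4–17 point amputation gap is not a bias: it is the difference between two quantities, freedom from amputation and freedom from amputation or death.

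This is a low-priority improvement to descriptive outcomes that drive no decision in the trial.

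**What to change.** Replace the Kaplan-Meier sentence with text along these lines: cumulative incidence of re-intervention and of loss of patency will be estimated by the Aalen-Johansen method, with death and major amputation of the treated limb as competing events; amputation-free survival, defined as time to the first of major amputation or death, will be estimated by Kaplan-Meier and labelled as such; all will be reported with 95% confidence intervals at 1 year.

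The cost is a sentence or so in the analysis section, slightly more analysis work in standard software, and an amputation figure that looks less favourable because deaths count in it.

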**Methods and analysis:**

A single-arm phase II trial will be performed in 20 patients with acute peripheral arterial occlusions eligible for thrombolytic treatment. Low-dose catheter-directed thrombolysis with urokinase will be used. The investigated treatment will be performed during the first hour of thrombolysis, consisting of intravenous infusion of 4 Luminity phials (6 mL in total, diluted with saline 0.9% to 40 mL total) of microbubbles with the use of local ultrasound at the site of occlusion. Primary end points are the incidence of complications and technical feasibility. Secondary end points are angiographic and clinical success, duration of thrombolytic infusion, treatment-related mortality, amputations, additional interventions and quality of life.

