**Trial registration numbers:**

Dutch National Trial Registry: NTR4731; European Clinical Trials Database of the European Medicines Agency: 2014-003469-10; Pre-results.

Strengths and limitations of this studyThis will be a first in man study to examine the safety and technical feasibility of therapeutic microbubbles, combined with the application of ultrasound and catheter-directed thrombolysis in peripheral arterial occlusions.This is a ‘single-arm’ trial. The data will be used to inform a future large multicentre randomised controlled trial comparing conventional catheter-directed thrombolysis with Microbubble and UltraSound-accelerated Thrombolysis.The present study is a non-randomised phase II trial; therefore, the results cannot confirm benefit of sonothrombolysis for peripheral arterial occlusions, only safety and feasibility is analysed.The present study does not compare other thrombolysis techniques or protocols.

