### Design

The Microbubbles and UltraSound-accelerated Thrombolysis (MUST) trial is a single-arm phase II trial.

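### Group-comparison tests and a blanket p<0.05 are set for a one-arm trial of 20 with no groups named, and no listed method addresses the primary end points or the aim of SAEs below 20%

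*Protocol article*

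**What the plan says.** All places are in the protocol article.

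- **Design:** "The Microbubbles and UltraSound-accelerated Thrombolysis (MUST) trial is a single-arm phase II trial".
- **Patients and eligibility criteria:** "We chose a sample size of 20 to assess the safety of the investigational treatment". The reason given just before is "Usually, in a phase II trial 10–20 patients are investigated to confirm an occurrence of toxic effects or SAEs<20" per cent. This is the only numerical aim for safety.
- **Abstract, Methods and analysis:** "Primary end points are the incidence of complications and technical feasibility". Under Primary study parameters, feasibility means carrying out the experimental procedure in the first hour, a yes/no result per patient. SAEs are defined there without requiring a relation to treatment.
- **Strengths and limitations:** "the results cannot confirm benefit of sonothrombolysis for peripheral arterial occlusions, only safety and feasibility is analysed".
- **Statistical analysis:** "Categorised epidemiological/descriptive patient variables are summarised with frequencies and will be analysed with" Fisher's exact or Pearson's chi-square test. The section goes on to Spearman and Mann-Whitney for skewed data, correlation or regression for pairs of outcomes, and Kaplan-Meier curves for patency, amputation and further intervention. It adds chi-square tests of heterogeneity in prognostic factors as a secondary analysis, and closes with "All tests will be performed two-sided, and p<0.05 will be considered to be statistically significant".
- **Discussion:** outcomes will be discussed against a historic control group. An application for a randomised trial follows if safety and feasibility are shown.

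**The concern.** Fisher's, chi-square and Mann-Whitney tests need at least two groups. The trial has one arm, and the section names neither the groups nor the prognostic factors. Both primary end points are single proportions out of 20, and the 20% figure is a ceiling on one of them. The section does not mention these end points, and none of its methods places a proportion against a ceiling.

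What is at stake is how the result is read. An observed 1/20 or 2/20 lies below 20% and could be reported as confirming the aim, although data of that size leave rates well above 20% open. That statement would then support the step to the randomised trial described in the Discussion.

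**Working it through.** **Inputs.** From the protocol article: n = 20 in one arm; ceiling 20%; two-sided 0.05; major haemorrhage in up to 8% of patients under thrombolysis (Introduction). Assumed here: 95% confidence, to match the two-sided 0.05; true SAE rates of 2% to 10%; and, for step 6 only, a 10 v 10 split.

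**1. Methods against questions.**

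| Method listed | Usable in one arm? | Addresses SAE <20% or feasibility? |
|---|---|---|
| Fisher, chi-square, Mann-Whitney | Only between subgroups; none named | No |
| Spearman, regression | Yes | No |
| Kaplan-Meier | Yes | No; the three outcomes named are not primary |

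**2. The plan's own figure.** The sample size comes with no error rate, power, expected rate or confidence level, so 20 cannot be strictly reproduced. As a plausibility check, the chance of no SAE when the true rate is 20% is 0.8^n:

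- n = 10: 0.107
- n = 14: 0.044
- n = 17: 0.0225
- n = 20: 0.0115

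With zero events, 14 patients suffice at one-sided 0.05 and 17 at one-sided 0.025. Twenty is therefore compatible with the aim if no SAE occurs. Ten, the lower end of the range given, is not: 0/10 has a 95% upper limit of 30.8%.

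**3. SAE proportion, exact (Clopper-Pearson) 95% interval.** The upper limit is the p that solves P(X ≤ x | 20, p) = 0.025. For x = 0 this is 1 − 0.025^(1/20) = 0.168.

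| SAEs | Observed | 95% interval |
|---|---|---|
| 0/20 | 0% | 0 to 16.8% |
| 1/20 | 5% | 0.1 to 24.9% |
| 2/20 | 10% | 1.2 to 31.7% |
| 3/20 | 15% | 3.2 to 37.9% |

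Only 0/20 excludes 20%. A one-sided 95% bound does not change this, since at 1/20 it is 21.6%. If the true rate were 20%, at most one SAE would occur with probability 0.069 and at most two with probability 0.206.

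**4. Feasibility, same method.** For 20/20 the lower limit is 0.025^(1/20) = 83.2%. For 19/20 it is 75.1%, and for 18/20 it is 68.3%. The article states no target proportion.

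**5. Chance of 0/20 at a true rate p, (1 − p)^20.**

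- 2%: 0.67
- 5%: 0.36
- 8%: 0.19
- 10%: 0.12

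**6. What a listed test would give.** With the assumed 10 v 10 split, Fisher's test gives p = 0.087 for 0 v 4 events and p = 0.033 for 0 v 5. These p-values compare the two halves with each other. They say nothing about whether the overall rate is below 20%.

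**The case against.** The strongest objection is that a journal article condenses the plan, so intervals for the primary end points may stand in a full protocol or SAP that is not shown. Silence alone would be no finding. But the section is not merely silent: it selects group tests, applies them to descriptive variables and sets a significance rule for all tests, and this selection does not fit the stated design and aim.

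Three stronger readings are tempting, and the article does not support them.

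- **That the primary end points get no estimate.** The abstract names an incidence and feasibility is yes/no per patient, so observed proportions are implied. What is absent is the interval and the criterion.
- **That there is no control at all.** The Discussion has a historic group. It is there for discussion only, with no test stated and an admission that efficacy cannot be adequately compared, so it does not supply the groups for the listed tests.
- **That the primary question cannot be answered.** The counts will exist, and exact intervals can be computed from them.

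It is also fair that Spearman, regression and Kaplan-Meier work in one arm. Subgroup tests are legitimate too, and the eligibility table offers natural splits such as native artery or bypass graft. The article presents 20% as customary in phase II, not as a formal hypothesis. The interim review after 10 patients and the stopping counts under Adverse events exist, but they are monitoring rules and not an analysis of the primary end points.

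**Conclusion.** The point holds in this limited form. The section sets group tests and a general p<0.05 without naming groups, and links no method to either primary end point or to the 20% aim. In numbers, 1/20 and 2/20 leave rates up to 24.9% and 31.7% open, and only 0/20 supports a claim of less than 20%. This rests on 20 evaluable patients, one yes/no SAE result per patient, 95% exact limits, and reading the 20% as a ceiling to be confirmed. If 20% is only background to the choice of sample size, the intervals are still needed to show precision, but the pass/fail reading falls away.

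**What to change.** Change the Statistical analysis section as follows.

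- Report the proportion of patients with an SAE, as defined under Primary study parameters, with an exact (Clopper-Pearson) 95% interval. Give treatment-related SAEs as an additional line, so that the numerator is not narrowed unnoticed.
- Report the proportion completing the first-hour procedure with the same kind of interval.
- State that a rate below 20% is claimed as confirmed only if the upper limit is below 20%. Otherwise describe the result as an estimate with its precision.
- Describe baseline variables without p-values.
- Name the factor for any subgroup test. Label all remaining tests exploratory and remove the p<0.05 rule.

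**Cost.** A paragraph of wording and no new data. Two consequences should be disclosed. At n = 20 a single SAE prevents the claim, and the chance of 0/20 is 0.36 at an assumed true rate of 5% and 0.19 at 8%. There would also be no significant secondary results to report.
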